## Abstract

**Background:** The morphology and functional severity of coronary stenosis show poor correlation. However, in clinical practice, the visual assessment of the invasive coronary angiography is still the most common means for evaluating coronary disease. The fractional flow reserve (FFR), the coronary flow reserve (CFR), and the resting full-cycle ratio (RFR) are established indices to determine the hemodynamic significance of a coronary stenosis.

**Design/Methods:** The READY register (NCT04857762) is a prospective, multicentre register of patients who underwent invasive intracoronary FFR and RFR measurement. The main aim of the registry is to compare the visual estimate of coronary lesions and the functional severity of the stenosis assessed by FFR, as well as the RFR pullback. Characterizations of the coronary vessel for predominantly focal, diffuse, or mixed type disease according to visual vs. RFR pullback determination will be compared. The secondary endpoint of the study is a composite of major adverse cardiac events, including death, myocardial infarction, and repeat coronary revascularization at 1 year. These endpoints will be compared in patients with non-ischemic FFR in the subgroup of cases where the local pressure drop indicates a focal lesion according to the definition of ΔRFR > 0.05 (for <25 mm segment length) and in the subgroup without significant ΔRFR. In case of an FFR value above 0.80, an extended physiological analysis is planned to diagnose or exclude microvascular disease using the CFR/FFR index. This includes novel flow dynamic modeling for CFR calculation (CFR_p−3D_).

**Conclusion:** The READY register will define the effect of RFR measurement on visual estimation-based clinical decision-making. It can identify a prognostic value of ΔRFR during RFR pullback, and it would also explore the frequency of microvascular disease in the patient population with FFR > 0.80.

**Clinical Trial Registration:**
ClinicalTrials.gov (NCT04857762).

## Background

The functional assessment of coronary artery lesions plays an increasingly important role in the clinical decision-making process involving patients with chronic coronary syndromes (CCS). According to the current European Society of Cardiology (ESC) guideline on coronary revascularization, pressure-wire derived fractional flow reserve (FFR) measurement is recommended in patients with a 40–90% diameter stenosis on visual angiographic estimation and without prior evidence of ischemia (1). The latest ESC guideline on CCS also suggests the use of non-hyperemic instantaneous wave-free ratio (iFR) as an alternative of FFR for cardiovascular risk stratification and for the indication of revascularization (2). The current American guideline includes the diastolic pressure ratio (dPR) and the resting full-cycle ratio (RFR) as further non-hyperemic indices, to aid clinical decisions (3). Data are still lacking regarding the relation of visual assessment and RFR measurements.

Non-hyperemic parameters have the potential for (co)localizing the pressure drop(s) related to significant coronary lesion(s) during a pullback measurement along a coronary artery without adenosine administration (4, 5). Advantages of the recently developed RFR include the detection of the highest resting differences between proximal and distal pressures during the cardiac cycle. In contrast to iFR, RFR determines the gradient not only in a specific phase of the diastole. This offers potential benefits especially at gradient detection in the right coronary artery (6–8).

In recent years, the importance of intracoronary pressure conditions along the epicardial vessels has been increasingly recognized.

The prognostic importance of the definition of focal pressure drop was highlighted in the EMERALD study (NCT02374775), where the authors defined a ΔFFR_CT_ cut-off of 0.06 providing the most valuable information for the prediction of acute coronary events. Possible explanation can be according to the authors, that the large pressure drop across the lesion causes large net force acting on the plaque, which may facilitate plaque rupture (9).

Such a prognostic pressure-drop cut-off value for invasive hyperemic or non-hyperemic pullback measurements has not yet been established. We defined the focal disease criterion as ΔRFR >0.05 for <25 mm segment length which is the same gradient for a 1 mm unit (>0.002/mm), similarly as it was defined for the iFR. We set out to test this threshold for prognostic value in our registry during the follow-up of patients with negative FFR but positive focal ΔRFR (4).

While the main aim of the READY registry is to characterize the effect of RFR measurement on the visual estimation-based clinical decision-making, it may also provide guidance in cases with a non-ischemic FFR but with focal pressure drop (ΔRFR > 0.05).

We plan to analyze the follow-up data at 1 year not only according to the pre-specified categories but also to determine potential alternative cut-off values using receiver-operator characteristic (ROC) analysis. In addition, it will also explore the frequency of microvascular disease in the patient population with FFR > 0.80.

## Study Objectives and Design

The “*Anatomical assessment vs. pullback REsting full-cycle rAtio measurement for evaluation of focal and Diffuse coronarY disease (READY)*” register is an investigator-initiated, prospective, and multicentre observational study. Three hundred patients with coronary stenoses between 40 and 90% in diameter and clinical indication of intracoronary physiological assessment are planned to be included.

The study is approved by the Hungarian Institution of Pharmacy and Nutrition (OGYÉI/61148/2018) and registered on the ClinicalTrials.gov (NCT04857762). All the included patients will sign an informed consent form to participate in the registry. Execution of the study is supported by an unrestricted grant provided by the PremierGMed Cardio Ltd.

### Inclusion Criteria

Written, informed consent from all patients should be obtained for the enrolment of their details into the database of the Registry for potential future analysis.

Patients with CCS, who require functional intracoronary assessment with pressure guidewires, as part of the clinical management of their condition, are eligible to enroll if the stenosis in one main coronary branch is assessed to be in the 40–90% range of diameter reduction on the invasive coronary angiography.

### Exclusion Criteria

Patients with acute coronary syndrome, left main disease, contraindication for adenosine, coronary artery bypass graft on the investigated vessel, severe renal insufficiency (estimated glomerular filtration rate <30 ml/min/1.73 m^2^), any medical comorbidity resulting in life expectancy <12 months are excluded.

### Angiographic Evaluation Protocol

Coronary diagnostic angiography is performed according to routine clinical practice. The visual estimate of the diameters stenosis % of the culprit lesion(s) should be included prospectively in the modified Syntax segmentation scheme (https://coronart.hu/), where the corresponding ventricular segments supply is indicated on a polar map (Figure 1). At the same time, the operator is required to record the characteristics of the coronary vessel disease as focal, diffuse, or mixed type, and to document their plan for angioplasty on the basis of the visual assessment.

**Figure 1 F1:**
[figure not shown]
Definition of the investigated coronary segments and the corresponding left ventricular segments on the polar map.

### Invasive Coronary Physiology Assessment Protocol

PressurewireX will be advanced distally to the investigated lesion(s) of a coronary artery. Resting and hyperemic average pressures will be determined in this distal position (in FFR mode). Hyperemia will be induced by 200 μg intracoronary adenosine injection.

A resting manual pullback with 1–2 mm/s speed will be performed (in RFR mode) under simultaneous fluoroscopic control.

The lesion length can be measured exactly by 3D coronary reconstruction from two appropriate angiographic projections at least 25° apart. In case of incorporated 3D reconstruction software (e.g., PieMedical to the Canon or Siemens systems) this 3D measurement can be performed promptly. Alternatively, 2D measurement can be done from the best projection with minimal foreshortening.

The co-registration of the coronary angiography and the pressure pullback trace of the RFR measurement is based on the simultaneous fluoroscopic acquisition of the pressure wire position and the pressure trace. Using a reference image together to the pullback of the pressure wire under fluoroscopy can indicate quite precisely the beginning and the end of the lesion can be marked simultaneously on the Quantien equipment by the Marker function. The difference between the distal and the proximal value of the RFR markers will be used in the calculation of the Δ*RFR* (Figure 2).

I. The main aims of the READY register and its **primary endpoints:**

**Figure 2 F2:**
[figure not shown]
RFR pullback investigation in the left circumflex artery with intermediate stenoses. Both lesions proved to be significant according to the local ΔRFR.

Our main aim is to compare the visual estimate of coronary lesions and the functional severity of the stenosis assessed by RFR pullback both on lesion and vessel levels.

Primary endpoint:

Characterization of the coronary vessel for predominantly focal/diffuse or mixed type disease according to visual vs. RFR pullback determination.

**Focal disease**: ΔRFR > 0.05 for <25 mm segment length (>0.002/mm)

**Diffuse disease**: ΔRFR > 0.05 for >25 mm segment length

If both the focal and diffuse criteria are fulfilled in the investigated vessel, then mixed type disease is diagnosed (Figure 2).

**II. Secondary endpoints:**
The therapeutic strategy (conservative/PCI/CABG) will be compared based on visual evaluation vs. RFR measurements (Figure 3).

**Figure 3 F3:**
[figure not shown]
Flow chart of the comparison of the visual assessment and the results of the RFR measurement.

Secondary endpoints in the subgroup of patients with negative FFR:

2. Secondary endpoint is defined only in the subgroup of patients with negative FFR as a composite of major adverse cardiac events, including death, type 1 myocardial infarction and coronary revascularization on the target vessel at 1 year. Type 1 myocardial infarction of the target vessel is defined according to the ESC classification (10). Revascularisation of the target vessel considered to be the composite secondary endpoint during the follow up.3. Clinical endpoints will be compared in patients with non-ischemic FFR and the subgroup of cases where the local pressure drop indicates a focal lesion according to the definition of ΔRFR > 0.05 (for <25 mm segment length), and the subgroup without significant ΔRFR.4. In the extended physiological sub-study, in cases where information regarding the microvascular state is desirable (i.e., patients with non-pathological FFR), the intracoronary average pressure values and the data of the 3D coronary reconstruction will be used for the calculations of coronary flow reserve (CFR) and the microvascular resistance reserve (MRR) (11–14). The rate of microvascular dysfunction will be determined in the investigated patient population (Figure 4).

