In our study, we defined the focal disease criterion as ΔRFR > 0.05 for <25 mm segment length, which is the same gradient for a 1 mm unit (>0.002/mm), as was used for the iFR. Nevertheless, we decided to work with a longer segment length, corresponding to current stent practices using deliberately longer stents.

The non-hyperemic determination of the resting pressure gradient by pullback measurement has also the advantage of simplifying the prediction of the stent implantation's effect. In contrast to the hyperemic FFR measurement, in resting condition there is no cross-talk between the physiological effect of the target lesion and the rest of the vessel. As the resting flow will not be changed after stent implantation in most cases, the effect of eliminating the specific resistance of the vessel can be predicted straightforwardly (5).

In this prospective registry, we aim to evaluate the additive value of intracoronary physiological measurements on clinical decision-making compared to visual estimation alone. We propose a flow-chart of the clinical decision-making process according to the results of physiological measurements (Figure 5). Hyperemic FFR measurement is intended to reflect the ischemia-inducing capability of the vessel. Furthermore, the characterization of the lesions to focal, diffuse or mixed types according to the RFR pullback has an important potential to influence the choice of treatment.

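### The FFR-negative composite counts any target-vessel revascularisation, so an arm difference may partly reflect clinicians acting on ΔRFR; separately, the abstract defines the composite differently

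*Protocol article*

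**What the plan says.** All references are to the protocol article.

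- **Endpoint (Secondary endpoints, item 2).** In patients with negative FFR the composite is "major adverse cardiac events, including death, type 1 myocardial infarction and coronary revascularization on the target vessel at 1 year". A further sentence says: "Revascularisation of the target vessel considered to be the composite secondary endpoint during the follow up". The MI component is tied to the target vessel and to the ESC classification.
- **Arms (Secondary endpoints, item 3).** FFR-negative patients "where the local pressure drop indicates a focal lesion according to the definition of ΔRFR > 0.05 (for <25 mm segment length") are compared with those without a significant ΔRFR. Statistical Analysis plans Kaplan-Meier curves and a log-rank test for these two groups. It also plans a ROC analysis with ΔRFR as predictor of a secondary endpoint at 1 year.
- **Availability of ΔRFR (Invasive Coronary Physiology Assessment Protocol).** Lesion limits are set during the pullback: "the end of the lesion can be marked simultaneously on the Quantien equipment by the Marker function". ΔRFR is the difference between the RFR values at those markers.
- **Link to treatment.** The first secondary endpoint reads: "The therapeutic strategy (conservative/PCI/CABG) will be compared based on visual evaluation vs. RFR measurements". The Discussion says that typing lesions as focal, diffuse or mixed "according to the RFR pullback has an important potential to influence the choice of treatment".
- **Abstract.** The composite there is a set of major adverse cardiac events "including death, myocardial infarction, and repeat coronary revascularization at 1 year".

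**The concern.** There are two separate defects.

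**1. The exposure can lead to the outcome without any biological effect.** The register examines whether RFR information changes treatment. It then counts one such treatment, revascularisation of the target vessel, as an adverse event in a comparison whose arms are defined by the same RFR information. More events in the focal arm could mean that a focal pressure drop marks a vulnerable plaque. They could also mean that a clinician who knew of the drop was readier to treat it. The composite as defined cannot separate the two. Yet the Abstract, Background and Discussion present this comparison as the test of the prognostic value of ΔRFR. The ROC cut-off is open to the same problem, because the predictor can prompt the outcome it is meant to predict.

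**2. Which events count is not settled.** The abstract has any myocardial infarction and repeat coronary revascularisation in any vessel. The endpoint section has type 1 infarction and target-vessel revascularisation. Repeat also does not fit an FFR-negative patient who has had no earlier revascularisation. This defect changes event counts; it does not create the bias in point 1.

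**Working it through.** **Step 1: the plan's own figure.** Statistical Analysis asks for 425 patients, with 10% vs 2% event rates, p < 0.05 and 80% power. It gives no arm ratio. A two-sided, continuity-corrected comparison of two proportions at an assumed focal to non-focal ratio of 1:4 (r = 4) reproduces it:

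- Mean risk: (0.10 + 4 × 0.02)/5 = 0.036.
- Uncorrected focal arm: n = [1.960 √(5 × 0.036 × 0.964) + 0.842 √(4 × 0.10 × 0.90 + 0.02 × 0.98)]² / (4 × 0.08²) = 69.6.
- Corrected: (n/4) × [1 + √(1 + 2 × 5/(n × 4 × 0.08))]² = 84.5, rounded up to 85.
- Total: 85 + 4 × 85 = 425.

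The ratio and the correction are assumptions. The result is used only to choose one pair of arm sizes, 85 vs 340.

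**Step 2: how much discretionary revascularisation would create the design contrast?** Suppose the true risk is 2% in both arms and a share q of focal patients is revascularised because of ΔRFR, independently of true risk. The focal arm reaches 10% when 1 − 0.98 × (1 − q) = 0.10, so q = 1 − 0.90/0.98 = 8.2%. About eight points therefore reproduce the planned 10% vs 2% with no prognostic effect.

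**Step 3: how often would the log-rank test be significant?** Simulation with exponential event times, 1 year of follow-up, two-sided 0.05 and 2% risk in the non-focal arm. The focal arm has 2% plus the added points. The 30 vs 120 split is a smaller assumed example at the same 1:4 ratio. Ranges cover repeated runs.

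| Added points in focal arm | Focal risk | 30 vs 120 significant | 85 vs 340 significant |
|---|---|---|---|
| 0 | 2% | about 7% | about 3% |
| 3 | 5% | 22–24% | 35–36% |
| 5 | 7% | 37% | 63% |
| 8 | 10% | 54–56% | 88–89% |

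The first row matters. With 30 vs 120 and no added revascularisation, only 30 × 0.02 + 120 × 0.02 = 3 events are expected. The test then rejects in about 7% of studies, always towards harm in the focal arm. That part of the later rows is small-sample error, not revascularisation bias.

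**Step 4: the two composites side by side.**

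| Component | Abstract | Secondary endpoints, item 2 |
|---|---|---|
| Death | yes | yes |
| MI | any | type 1, target vessel |
| Revascularisation | repeat, any coronary vessel | target vessel |

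A type 2 infarction is an event under the first definition and not under the second. So is a repeat procedure on another vessel. A first revascularisation of the target vessel is an event under the second definition and, read literally, not under the first.

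**The case against.** Several objections have force, and they limit the point.

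- **Index procedures.** A reader might infer that PCI at the index procedure counts as an event. The text does not support this: it counts revascularisation during follow-up, which on a natural reading leaves the index procedure out. What remains open is a planned or staged procedure carried out after it.
- **Who knows ΔRFR later.** A reader might take it as documented that follow-up decisions are made knowing ΔRFR. No section says who decides later in the year. The Discussion sentence on treatment concerns the whole population, and the decision flow charts are not shown. Knowledge of ΔRFR is likely, given console marking and a strategy endpoint based on RFR, but it is inferred.
- **Condensed article.** Adjudication rules and reason-for-procedure fields may stand in the full protocol, and their absence here is not the finding. The finding concerns the definition that is printed, which states the revascularisation component twice without a qualifier.
- **The abstract.** Shortening type 1 MI to MI is a small matter, and the detailed section would ordinarily govern. This stands as to weight, but the scope of revascularisation differs as well.
- **Size.** The added points, the 2% common risk and the arm sizes are not in the documents. The simulation shows how sensitive the test is to such events, not how many there will be.
- **Direction.** If focal lesions are treated at the index procedure, later target-vessel events in that arm could fall. The bias need not favour a positive finding.

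**Conclusion.** The point holds in a limited form. Because the composite includes target-vessel revascularisation for any reason, and because ΔRFR defines the arms and is expected to guide treatment, a difference between arms may partly reflect clinicians acting on ΔRFR. It is not sufficient evidence of prognostic value, and neither is a ROC cut-off from the same endpoint. It would go too far to say that the focal arm will look worse for this reason, or that the mismatch with the abstract produces a false signal.

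Under the stated assumptions, three to eight added points take the chance of a significant log-rank result from about 7% to between 22% and 56% at 30 vs 120, and from about 3% to between 35% and 89% at 85 vs 340. The true size of the effect cannot be learned from the documents.

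The differing composites are a definite, separate inconsistency that must be reconciled. Both matters concern a secondary endpoint, but it is the one that carries the register's prognostic claim, so they should be corrected before analysis.

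**What to change.** 1. Use one composite in the abstract and in the endpoint section.
2. Report death or target-vessel type 1 MI separately beside the composite. Make any claim of prognostic value, including the ROC cut-off, depend on consistency with that result.
3. Record the reason for each follow-up revascularisation. Also report the composite counting only revascularisations prompted by new symptoms or newly documented ischaemia, with planned or staged procedures not counted as events. This is a rule for counting events, not for managing patients.
4. Show the analysis that excludes patients treated at, or planned from, the index procedure as a sensitivity analysis only.

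The cost is revised endpoint wording, one added data field and some extra tables. There are also statistical costs. Fewer events will count, so power falls, and death or MI alone may be too rare to be conclusive. The exclusion in step 4 selects on a decision made after ΔRFR is known and leaves focal patients whom operators chose not to treat, which is why it should not be the main analysis. The reason-based rule reduces the bias but does not remove it, since clinicians aware of a focal drop may investigate and refer more readily.

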### Statistical Analysis

Descriptive statistics are planned as mean and SD, median (interquartile range) of the measured RFR and FFR values. Categorical variables will be compared with the Pearson χ^2^ test for focal/ diffuse/mixed type categorizations of the coronary disease by visual and physiological evaluations.

Correlation among variables will be determined by calculating Spearman ρ correlation coefficient.

Kaplan-Meier curves will be used to graphically display adverse events by focal lesion (ΔRFR ≥ 0.05/ 25 mm) and without focal lesion (ΔRFR < 0.05/ 25 mm) arms in the cases with FFR > 0.80. We plan to use survival analytic techniques such as a log-rank test to estimate the difference between the 2 subgroups.

The required sample size for the statistically significant (*p* < 0.05) difference with 80% power of the Kaplan-Meier curves of adverse events by focal lesion (ΔRFR ≥ 0.05/ 25 mm) and without focal lesion arms are 425, assuming 10 and 2% event rate in the two subgroups, respectively.

ROC analysis will be used to determine an optimal clinical cut of value, of ΔRFR (together its sensitivity and specificity) to predict a secondary endpoint at 1 year.

All analyses will be performed by using the Medcalc statistical software (MedCalc Software Ltd, Belgium).

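### Target-vessel revascularisation counts as an adverse event whatever its reason, so procedures prompted by the index ΔRFR could inflate the focal arm

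*Protocol article*

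**What the plan says.** The composite for the FFR-negative subgroup is given in the protocol article under Secondary endpoints, item 2: "death, type 1 myocardial infarction and coronary revascularization on the target vessel at 1 year". The same item adds a counting rule: "Revascularisation of the target vessel considered to be the composite secondary endpoint during the follow up". Neither sentence limits the procedures by indication, symptoms, evidence of ischaemia, or whether they were already planned after the index measurement.

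The Abstract describes the endpoint as "major adverse cardiac events, including death, myocardial infarction, and repeat coronary revascularization at 1 year". That version adds the word repeat, drops the restriction to the target vessel, and also gives no indication.

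Item 3 and the Statistical Analysis section compare this outcome between patients with and without a focal ΔRFR (threshold 0.05 over 25 mm), using Kaplan-Meier curves and a log-rank test. A ROC analysis then seeks the ΔRFR cut-off that best predicts a secondary endpoint at 1 year.

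Three statements bear on whether ΔRFR can itself lead to a procedure:
- Invasive Coronary Physiology Assessment Protocol: the beginning and end of the lesion "can be marked simultaneously on the Quantien equipment by the Marker function", and ΔRFR is the difference between the marker values. No blinding is described.
- II. Secondary endpoints, item 1: "The therapeutic strategy (conservative/PCI/CABG) will be compared based on visual evaluation vs. RFR measurements".
- Discussion: characterising lesions as focal, diffuse or mixed "according to the RFR pullback has an important potential to influence the choice of treatment".

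**The concern.** The stated aim is to test whether a focal pressure drop has prognostic value when FFR is negative. That requires the outcome to arise independently of anyone having read the exposure. Death and infarction meet that requirement reasonably well. Revascularisation is a decision, and here it can be taken by people who know the ΔRFR that defines the arms.

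Suppose an operator sees a focal drop and arranges PCI or CABG for a later date. Under the counting rule as written, that procedure is an adverse event. It may also be the therapeutic strategy recorded for secondary endpoint 1. Such procedures would fall mainly in the focal arm. Restricting the comparison to vessels left untreated at the index session would not remove them, because they come later.

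At stake is the meaning of a positive result. A separation of the curves, or a ROC optimum near 0.05, could come from operators following the 0.05 rule with no difference in underlying risk.

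**Working it through.** **The plan's own figure.** The Statistical Analysis section asks for 425 patients, "assuming 10 and 2% event rate in the two subgroups, respectively", with p < 0.05 and 80% power. It states no allocation ratio, sidedness or correction. Assume a two-sided test and four non-focal patients per focal patient (k = 4):

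- Pooled rate = (0.10 + 4 × 0.02)/5 = 0.036.
- Focal n = [1.960·√(1.25 × 0.036 × 0.964) + 0.842·√(0.10 × 0.90 + 0.02 × 0.98/4)]² / 0.08² = 69.6, rounded to 70, for a total of 350.
- With continuity correction: n = (69.6/4)·[1 + √(1 + 2 × 5/(4 × 69.6 × 0.08))]² = 84.5, rounded to 85. The total is 85 + 340 = 425.

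The figure is reproduced, but the 1:4 ratio and the correction are assumptions. Without the correction, a 1:1 split gives 276.

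**How many prompted procedures equal the planned difference.** Let the true risk be 2% in both arms and let a share q of focal patients have a later procedure because of the index ΔRFR. The observed focal rate is 1 − 0.98·(1 − q). Setting this to 10% gives q = 1 − 0.90/0.98 = 8.2%. In 85 focal patients that is 85 × 0.082 ≈ 7 procedures. This equality holds by construction. It shows the scale and predicts nothing.

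**Chance of a significant result with no difference in underlying risk (normal approximation, 20% focal).** Power = Φ[(|p1 − p2| − 1.96·SE0)/SE1], with SE0 pooled and SE1 unpooled. For q = 5% at 85:340, p1 = 0.069, SE0 = 0.0206 and SE1 = 0.0285, so Φ[(0.049 − 0.0404)/0.0285] = Φ(0.30) ≈ 62%.

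| FFR-negative patients analysed | q = 2% | q = 5% | q = 8.2% |
|---|---|---|---|
| 425 | 23% | 62% | 86% |
| 300 | 19% | 51% | 75% |
| 150 | 14% | 35% | 54% |

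**Simulated log-rank test.** Exponential times to 1 year, 2% true risk in both arms, the triggered share added to the focal arm, 30% focal, two-sided 5%:

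| Triggered share | 0% | 1% | 2% | 3% | 5% | 8% |
|---|---|---|---|---|---|---|
| 150 patients | about 5% | 11% | 16% | 24% | 40% | 66% |
| 300 patients | about 5% | 13% | 22% | 34% | 58% | 86% |

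Repeat runs agree to within a few percentage points. With 150 patients and 30% focal there are 45 focal patients, so 1% to 8% is an expected 0.45 to 3.6 procedures. With so few events, a handful of procedures decides the test.

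The analysed numbers are assumptions too. Study Objectives and Design plans 300 patients at any FFR value, so 300 FFR-negative patients is an upper bound and 150 would be half of enrolment. No triggered share is given in the documents.

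**The case against.** Several parts of the opposing case stand.

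- **Knowledge and timing are inferred.** No sentence says that operators use ΔRFR when deciding on later procedures; this is read from the console marking and the expected influence on treatment. Nor does the article say when follow-up starts. A reader might infer that every CABG or deferred PCI automatically becomes an event. The text does not settle that, and the Abstract's word repeat points the other way, towards procedures after the index strategy. It does not resolve the matter, because the endpoint section words the component differently and neither version gives an indication criterion.
- **The treatment statements are general.** The strategy comparison covers all patients, including those with positive FFR, and the Discussion speaks only of potential. The decision flow charts (Figures 3 and 5) are not visible here and might make ΔRFR-prompted procedures rare when FFR is above 0.80. The counting rule would still include any that occur.
- **Direction.** A reader might infer that the bias must run away from the null. It need not: prompted treatment could lower later infarction or urgent revascularisation in the focal arm, and the calculations include no such offset.
- **Magnitude.** The triggered shares are assumed. A ROC simulation with a risk step placed at 0.05 returns 0.05 by construction, so it is no evidence about what this register would find.
- **Condensed article.** Adjudication and event forms may well be in the full protocol, and their absence is not the point. The article does state which target-vessel revascularisations count, and it sets no condition.

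**Conclusion.** The concern holds as a weakness in a stated endpoint rule. As written, the exposure that defines the arms can trigger a component of the outcome, and the Abstract and the endpoint section do not agree on that component. The focal versus non-focal comparison and the ROC cut-off could then partly measure operators' response to ΔRFR. If even 1% to 8% of focal patients had such a procedure, the false-positive rate at 150 FFR-negative patients would rise from 5% to roughly 11% to 66%. This assumes 30% focal, equal 2% risks and no protective effect of the prompted treatment. The actual frequency is unknown and the net direction is not certain.

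This should be fixed, but it does not undermine the register. It concerns one component of a secondary endpoint in a subgroup. The mechanism does not inflate death or infarction. The primary endpoint, the strategy comparison and the microvascular sub-study are unaffected. The documents also do not support the inference that the planned 10% versus 2% contrast is itself an artefact.

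**What to change.** 1. Reconcile the Abstract with Secondary endpoints, item 2: target vessel or any vessel, repeat or any procedure, and when follow-up starts.
2. Record the therapeutic strategy after the index measurement, and the reason for each later revascularisation when it happens.
3. Count target-vessel revascularisation only if it was outside that recorded strategy and clinically prompted: new or worsening symptoms, objective ischaemia or infarction. Fix the definition before outcomes are reviewed and, where possible, have events classified without knowledge of ΔRFR, since operators who know it would otherwise supply the reason.
4. Treat planned or ΔRFR-prompted procedures as a competing event in the main time-to-event analysis, with cumulative incidence curves. Keep censoring at the procedure as a sensitivity analysis only, because that censoring depends on the exposure and is informative.
5. State how patients with such a procedure enter the ROC analysis, whose outcome is binary at 1 year.
6. Report death plus type 1 target-vessel infarction separately, and the all-revascularisation composite as a sensitivity analysis.

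These changes concern what is counted and analysed, not which vessels are treated. The cost is revised endpoint wording, the strategy and reason entries on the case report form, and some classification effort. The downside is fewer countable events and less precision. Reasons reconstructed later from records would be less reliable than reasons recorded prospectively.
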